### Monitoring treatment attendance and adherence

#### Treatment attendance

For both treatment arms, attendance at treatment sessions is monitored via completion of a treatment attendance form following all scheduled treatment sessions. This form records the participants’ attendance and reasons for non-attendance and participant withdrawal from treatment (either by the therapist or participant themselves), concomitant treatments and whether the participant has been referred on for other treatment.

#### Treatment adherence and integrity

In addition to the treatment attendance forms, for each treatment session attended, a session rating form is also completed by the treating physiotherapist or psychologist. These forms have been designed to ascertain which components of the treatments were covered and are specific to the treatment arm. In the CCBT arm, all sessions will also be audio-taped and a sample of these coded by an independent reviewer, using an agreed rating scale developed by the CCBT expert. To ensure treatment adherence in the TAU arm, a sample of the physiotherapy classes will be observed by the physiotherapy expert and the components covered recorded.

### Sample size

We plan to recruit 92 participants in total, randomised equally to the TAU and CCBT arms. As this is a feasibility study, formal power calculations are not appropriate, as the study is not designed to test for a difference between treatments. Recommendations for feasibility studies propose that the analysis dataset comprises a minimum of 30 participants for each arm in order to estimate parameters for future sample size calculations [32-34]. We anticipate that the combined total of non-compliance and loss to follow up will be no more than 35% (that is, 25% due to loss to follow up and 10% due to non-compliance) and therefore, aim to recruit 46 patients in each arm, to account for potential missing data. Part of the rationale for a feasibility study is to gather data to inform the design of a definitive study; hence, estimates for non-compliance and loss to follow up rates in this patient group will be generated by the end of the study and will feed into power calculations for the full trial.

### Planned analyses

The analyses will be descriptive in nature and provide estimates of key trial parameters for the definitive RCT. A combination of qualitative and quantitative measures will be used to address the research questions relating to the acceptability and credibility of CCBT and the feasibility of conducting a definitive trial in the future. Statistical analyses will be on an intention-to-treat basis with participants being analysed according to their randomisation allocation. Data will be analysed at the end of the study when all data collection, entry and validation is completed. There are no planned sub-group analyses. As this is a feasibility study, analysis will focus on confidence interval estimation, rather than hypothesis testing. Credibility data (expectation and satisfaction) will be summarised by group and centre, together with 95% confidence intervals. The number of participants missing sessions, and withdrawal (from treatment, follow up or both) in each arm will be reported overall, by centre and by therapist.

The success of recruitment strategies will be measured by summarising eligibility, consent and randomisation rates, both overall and by centre. The burden of measurement tool completion will be assessed by summarising follow up rates and the time taken at baseline and follow up for completion of the measurements. The level of missing data (for individual items and for entire outcome measures) will also inform the assessment of measurement tool acceptability.

Qualitative analyses will be carried out independently by two researchers on transcripts from the interviews conducted with consenting patients in each treatment condition. We will use directed content analysis [35] to explore consensus, and present the analysis backed by verbatim quotes to illustrate main points. Errors, omissions and commission will be discussed and resolved between the researchers.

To investigate the process of change and to generate evidence of proof of principle, we will report mean change from baseline in the three-month CPAQ scores separately for the randomised groups with their 95% confidence intervals. CCBT is expected to show a greater change in the CPAQ than TAU. In addition, we use exploratory plots and measures of correlations to investigate the relationship between levels of change in acceptance and disability at follow up.

Secondary outcome measures relating to quality of life, mood, pain and global recovery post-treatment at six months will be summarised by point estimates, variability estimates and 95% confidence intervals presented by randomised group at each time point.

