### Aims and objectives

The aim of this study is to test the acceptability and credibility of CCBT against best-practice physiotherapy (treatment as usual (TAU)) for people with chronic back pain with associated avoidance of daily activities. In addition, we aim to test the feasibility of implementing a full scale RCT.

The primary objectives are:

•To determine whether CCBT is an acceptable and credible intervention for NHS patients with persistent back pain and avoidance in comparison to TAU

•To assess recruitment processes and study uptake to inform the feasibility of a definitive RCT

•To assess follow up response rates and level of missing data

•To assess the burden of measurement tool completion

•To demonstrate proof of principle by gathering information about the process of change between the two treatment arms (that is, whether the effect of CCBT in enhancing acceptance post-intervention is sufficiently promising compared to the control to warrant a full trial)

The secondary objectives are to measure long-term changes in quality of life outcomes relating to mood, pain, disability and functioning.

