### Settings and participants

A total of 92 participants will be recruited from four NHS musculoskeletal/physiotherapy services who have agreed to take part in this study. Patients meeting the following criteria are eligible for study entry:

•Over 18 years of age

•Suffering from chronic lower back pain of at least three months duration

•Suitable for physiotherapy-led treatment

•Not requiring referral to any other department/service

•Classified as avoidant (defined as endorsing any of the three psycho-social questions from the high-risk sub-group on the Sub-groups for Targeted Treatment for Back Pain Screening Tool (STarT Back) [16] and a score of 38 or more on the Tampa Scale for Kinesiophobia (TSK) [17]

Patients meeting any of the following criteria will not be eligible for study entry:

•Currently receiving psychological treatment

•Presence of sciatica (burning throbbing and radiating leg pain of spinal origin confirmed by performing the straight-leg raise test)

•Presence of a progressive disorder (for example, chronic obstructive pulmonary disease (COPD), cardiovascular disease, rheumatoid arthritis, lupus, ankylosing spondylitis and neoplastic disease)

•Pregnancy

•Insufficient proficiency in English to comply with treatment or provide data

•Involved in ongoing litigation relating to the pain condition

Determining eligibility for participation will be a multi-stage process; some of the eligibility criteria are established upfront during review of the referral by the on-duty physiotherapist (for example, age, duration of symptoms), others during review of the completed screening questionnaire, telephone contact with the patient or during the physiotherapy assessment. Rates of referrals, eligibility, consent, and randomisation are monitored at each stage to assess trial uptake.

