### Randomisation

Participants will be randomised on a 1:1 basis to receive either CCBT or TAU and will be stratified by centre and pain interference score [19-21]. Randomisation will occur through the Clinical Trials Research Unit (CTRU) 24-hour automated randomisation system.

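### The first primary objective compares credibility with TAU, but the stated credibility analysis names no between-arm difference

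*Protocol article*

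**What the plan says.** In Aims and objectives, the first primary objective reads: "To determine whether CCBT is an acceptable and credible intervention for NHS patients with persistent back pain and avoidance in comparison to TAU". It is therefore comparative.

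Primary and secondary outcomes measures credibility to patients in three ways: two prospective questions on expectation before treatment, the original credibility questionnaire at three months (satisfaction), and a patient interview at three months. Table 1 puts expectation at baseline. Participant identification and recruitment process says that baseline data are gathered before randomisation.

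Planned analyses gives one sentence to the questionnaire data: "Credibility data (expectation and satisfaction) will be summarised by group and centre, together with 95% confidence intervals". The same section describes the analyses as descriptive, by intention to treat, and aimed at interval estimation instead of testing. It reports missed sessions and withdrawal by arm, and it plans qualitative analysis of interviews from both arms.

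**The concern.** The objective asks how CCBT stands against TAU, and the stated output is a set of separate intervals. A between-arm difference with its own interval is the quantity that answers a comparative question, and randomisation is what makes that quantity interpretable. It is not named for the lead objective.

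Two features add to this. First, the phrase on group and centre does not say whether the two factors are crossed. If they are, the output is eight small cells, and wide intervals for single cells invite readers to interpret chance differences between centres. Second, expectation and satisfaction are treated alike, although they differ in kind. Expectation is recorded before allocation, so a gap between arms shows only how the randomisation fell. Satisfaction is recorded after treatment and can differ because of it.

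At stake is how clearly the study reports relative credibility, which is one of the inputs to the decision on a definitive trial.

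**Working it through.** **Inputs from the article**
- Settings and participants: "A total of 92 participants will be recruited from four NHS musculoskeletal/physiotherapy services".
- Randomisation: "Participants will be randomised on a 1:1 basis to receive either CCBT or TAU and will be stratified by centre"; pain interference score is the other stratification factor.
- Sample size: "aim to recruit 46 patients in each arm"; target for analysis "a minimum of 30 participants for each arm"; losses "that is, 25% due to loss to follow up and 10% due to non-compliance".
- The SD of the credibility score is not given, so precision is in SD units, with a common SD assumed.

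**The plan's own figure.** 30/(1 − 0.35) = 46.15, against 46 per arm in the plan. In reverse, 46 × 0.65 = 29.9. The figure is reproduced.

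**Numbers available for credibility**
- Expectation (baseline): 46 per arm.
- Satisfaction (three months, 25% loss): 46 × 0.75 = 34.5 per arm. Non-compliers stay in under intention to treat. If the full 35% were lost, 29.9 per arm remain.
- Crossed cells, equal recruitment at four centres: 92/(2 × 4) = 11.5 at baseline; 11.5 × 0.75 = 8.6 at 25% loss; 11.5 × 0.65 = 7.5 at 35% loss.

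**Formulas for the 95% half-width, in SD units**
- One mean: t(0.975, n − 1)/√n.
- Difference between two arms of n each: t(0.975, 2n − 2) × √(2/n).

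| | Baseline | 25% loss | 35% loss |
|---|---|---|---|
| Cell mean (crossed) | ±0.65 | ±0.79 | ±0.88 |
| Whole-arm mean (marginal) | ±0.30 | ±0.35 | ±0.37 |
| Within-centre arm difference | ±0.87 | ±1.02 | ±1.12 |
| Overall arm difference | ±0.41 | ±0.48 | ±0.52 |

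The comparison must be like with like: a cell mean against an arm mean (0.79 against 0.35), or a within-centre against an overall difference (1.02 against 0.48). Allowing for centre in the degrees of freedom leaves the overall figures unchanged to two decimals.

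**What comparison by eye costs, even on the marginal reading.** At 34.5 per arm, two arm intervals stop overlapping only when the means differ by 2 × 0.346 = 0.69 SD. The interval for the difference already excludes zero at 0.48 SD. For gaps between 0.48 and 0.69 SD, overlapping intervals would suggest less separation than the direct estimate shows.

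**The case against.** The strongest reply is that this is a descriptive feasibility study, in a condensed article, whose analysis plan is not shown. The sample size section says the study was not set up to test for treatment differences, and pain acceptance and the secondary outcomes are also reported by arm. A difference row or a covariate list is the kind of detail an analysis plan may add, and nothing in the article rules one out. This stands as far as it goes: a reader might infer that the randomised comparison has been excluded, and the text does not support that. But the article does fix the form of the output for its lead objective, and that form does not match the objective. Declining tests does not explain the gap, because a difference with a 95% CI is itself interval estimation.

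A reader might also infer that the output is definitely eight cells of about 11. The text does not establish this. The wording can mean by group and, separately, by centre. Neighbouring sentences mention overall results and this one does not, which favours crossing but does not settle it. Cell sizes also rest on equal recruitment.

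Nor is it right that the objective cannot be answered. Interviews in both arms, attendance and withdrawal also bear on it, and arm-level estimates let a reader work out a rough unadjusted difference. These fill the gap only in part.

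Finally, the added estimate would not show that the treatments are equally credible: no margin is stated, and ±0.48 SD is wide. Expectation is a named outcome, so summarising it by arm is legitimate description. Intervals at centre level are a matter of presentation.

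**Conclusion.** The point holds as an improvement that costs nothing, not as an error that undermines the study. A comparative primary objective has no stated between-arm estimate for its quantitative measure. This is so under either reading of the group-and-centre phrase; only the size of the separate intervals changes, from about ±0.35 SD for a whole arm to about ±0.79 SD for a crossed cell at three months.

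The comparison must rest on three-month satisfaction. This assumes that expectation is collected with the other baseline data, as Table 1 shows; the outcomes section says only that it precedes treatment. The figures assume 25% loss spread evenly over arms and centres, equal recruitment at the four centres for the cell sizes, and a common SD.

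**What to change.** In Planned analyses, add that the main quantitative credibility result is the overall CCBT minus TAU difference in three-month satisfaction with a 95% CI, by allocated arm, adjusted for baseline expectation, centre and pain interference score. State that it is an estimate and not a test. Expected precision is about ±0.48 SD unadjusted at 34.5 per arm. Any gain from adjusting for expectation depends on its correlation with satisfaction, which the article does not give, so none should be promised.

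Keep the by-arm and by-centre summaries as description, say whether they are crossed or marginal, and note that baseline expectation by arm describes balance and is not evidence on relative credibility.

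The cost is a few lines of analysis text. All the data are already collected, and sample size, visits and questionnaires do not change.

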**Methods/design:**

A feasibility study of a pragmatic randomised controlled trial comparing psychologist-delivered Contextual Cognitive Behavioural Therapy (CCBT) against Treatment As Usual (TAU) physiotherapy delivered by physiotherapists for the treatment of chronic lower back pain in ‘avoidant’ patients. Ninety-two patients referred for physiotherapy will be recruited and randomised on a 1:1 basis to receive CCBT or TAU. Treatment groups will be balanced by centre and pain interference score. Primary outcomes include assessing the credibility and acceptability of the intervention, and to demonstrate proof of principle through a greater change in pain acceptance in the CCBT arm, measured by the Acceptance and Action –II and the Chronic Pain Acceptance questionnaires. In addition, the feasibility of carrying out a full trial will be explored with reference to recruitment and follow-up rates including the assessment of the burden of outcome measure completion. Secondary patient outcomes include disability, pain, fear of movement, mood, quality of life, and global recovery. Outcomes are measured at three and six months post-randomisation.

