### Primary and secondary outcomes

The primary outcomes of interest include credibility and acceptability of CCBT in the treatment of back pain, and the feasibility of recruitment and completion of outcome measures to the trial. These will be assessed as follows:

•Credibility of treatment to patients

∘ First two modified (prospective) questions of the Borkovec and Nau questionnaire prior to treatment (expectation) [22]

∘ Original Borkovec and Nau questionnaire at three months (satisfaction) [22]

∘ Patient interview at three months: a qualitative semi-structured interview with the researcher.

•Acceptability of treatment to patients

∘ Number of sessions attended

∘ Reasons for early withdrawal from treatment

∘ Patient interviews at three months

•Acceptability and credibility of the treatment to therapists

∘ Interview at end of study

•Feasibility of recruitment process

∘ Number eligible for screening questionnaires

∘ Number of screening questionnaires completed and returned

∘ Numbers attending interview with researcher

∘ Numbers randomised entered into the trial

∘ Reasons for non-participation and ineligibility

∘ A comparison of the postal and in-clinic screening and recruitment methods

•Feasibility of assessment tools

∘ Time taken to complete questionnaires at all time points

∘ Number of missing items

∘ Follow up rates

∘ Patient interviews at three months - acceptability of measurement completion

•Proof of principle (process of change due to treatment)

∘ Chronic Pain Acceptance Questionnaire (CPAQ) [23] at three months

∘ Acceptance and Action Questionnaire-II (AAQ-II) [24] at three months

The secondary outcomes (measured at three and six months) include:

•Disability, measured by the Roland Morris Disability Questionnaire (RDQ) [25].

•Pain, measured by Brief Pain Inventory (BPI) [18-20]. Although CCBT does not aim to reduce pain, a measurement of pain is needed to test the randomisation process and be included as a covariate in the final analysis.

•Fear of movement, measured by the TSK [17]. The TSK measures the extent in which patients with chronic pain experience fear of movement or injury/re-injury.

•Mood measured using the Hospital Anxiety and Depression Scale (HADS) [26]

•Quality of life measured by the Euroquol 5D (EQ-5D™) [27,28] and the Short-Form 12 (SF-12V2™) [29].

•Recovery, measured by the Modified Patient Global Impression of Change (MPGIC) [30,31].

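### The proof-of-principle objective compares CCBT with TAU, but the planned CPAQ analysis gives each arm's change separately and no between-arm difference with its interval

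*Protocol article*

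**What the plan says.** Under Aims and objectives, one of the five primary objectives asks "whether the effect of CCBT in enhancing acceptance post-intervention is sufficiently promising compared to the control to warrant a full trial". The Methods/design paragraph of the abstract puts the same aim as "to demonstrate proof of principle through a greater change in pain acceptance in the CCBT arm" and names two measures, the AAQ-II and the CPAQ. Primary and secondary outcomes lists both, at three months, under proof of principle.

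The Planned analyses section then states the output: "we will report mean change from baseline in the three-month CPAQ scores separately for the randomised groups with their 95% confidence intervals". The next sentence gives a direction, "CCBT is expected to show a greater change in the CPAQ than TAU", without a difference, an interval for one, or an analysis of the AAQ-II. The plots and correlations that follow relate change in acceptance to disability and do not compare the arms. Secondary outcomes are also summarised by randomised group.

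Two other statements bear on this. Primary and secondary outcomes says a pain measurement is "needed to test the randomisation process and be included as a covariate in the final analysis". Randomisation says participants "will be stratified by centre and pain interference score". The analyses described are by-group summaries, with no model in which a covariate or a stratification factor could sit.

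**The concern.** The question concerns a contrast between randomised arms, while the stated output is two one-arm summaries. This is more than detail left to an analysis plan: the article names the output, and that output does not match the objective it is meant to serve.

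The result is meant to inform whether a full trial is warranted. A reader given two separate intervals will tend to compare them by eye, either by asking whether they overlap or by asking which one excludes zero. Neither gives the precision of the difference, and the two err in opposite directions. Any difference derived by hand from the published summaries would also lack adjustment for baseline CPAQ, pain interference and centre, although the design collects all three and balances allocation on the last two.

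**Working it through.** **Inputs from the article.** Sample size: at least 30 analysed per arm; 25% loss to follow-up plus 10% non-compliance, 35% combined; 46 recruited per arm, 92 in total. Randomisation: 1:1. Planned analyses: 95% intervals and analysis by allocated arm.

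**Assumptions.** The article gives no SD for CPAQ change, so results are in units of that SD, taken as equal in both arms. Intervals are two-sided and t-based.

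**The plan's own figure.** 30 / (1 − 0.35) = 46.15, stated as 46; and 46 × 0.65 = 29.9. The target reproduces to rounding. If only loss to follow-up removes patients, as analysis by allocation suggests, 46 × 0.75 = 34.5, so about 34 per arm.

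**Half-widths.** Within one arm: t(n − 1) / √n. Difference between arms: t(2n − 2) × √(2/n). Two within-arm intervals of equal width stop overlapping when the means differ by twice the within-arm half-width.

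| n per arm | Within-arm half-width | Half-width of the difference | Difference needed for non-overlap |
|---|---|---|---|
| 30 | 0.373 | 0.517 | 0.747 |
| 34 | 0.349 | 0.484 | 0.698 |
| 46 | 0.297 | 0.414 | 0.594 |

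At 30 per arm, the interval for the difference excludes zero once the observed difference passes 0.52 SD, while non-overlap needs 0.75 SD. On a normal approximation, non-overlap corresponds to a two-sided p of 2 × [1 − Φ(1.96 × 2/√2)] = 0.0056. Judging by overlap is therefore too strict.

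**Judging by which interval excludes zero.** Suppose both arms truly change by the same amount d. Let p be the chance that one arm's interval lies above zero (noncentral t, 29 degrees of freedom, noncentrality d√30). The chance that CCBT's interval does so and TAU's does not is p(1 − p).

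| d (SD of change, assumed) | p | CCBT alone | Exactly one arm, 2p(1 − p) |
|---|---|---|---|
| 0.2 | 0.184 | 0.15 | 0.30 |
| 0.3 | 0.355 | 0.23 | 0.46 |
| 0.36 | 0.479 | 0.25 | 0.50 |
| 0.4 | 0.563 | 0.25 | 0.49 |
| 0.5 | 0.754 | 0.19 | 0.37 |

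The product p(1 − p) cannot exceed 0.25, so the middle rows show the worst case. Over the assumed range, CCBT alone appears to change in about 15% to 25% of studies in which the arms do not differ.

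**The case against.** The strongest defence is that this is a feasibility study. The article declines a power calculation, says the study is not meant to test one treatment against the other, and promises estimation in place of testing. That rules out a demand for a test or for power. It does not explain the gap, because a difference with a 95% interval is itself estimation.

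Several stronger readings are tempting, and the article does not support them.

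- *The plan cannot answer its question.* It can, crudely. The arms are independent, so the means can be subtracted and the half-widths combined in quadrature: √(0.373² + 0.373²) = 0.53 SD at 30 per arm, close to the direct 0.52. What is missing is a stated, adjusted estimate.
- *The evidence would be an uncontrolled before-after change.* TAU is a concurrent randomised control and its change is reported beside that of CCBT. Natural recovery and regression to the mean affect both arms and cancel, in expectation, in the comparison.
- *The plan will judge by overlap or by an interval excluding zero.* It states neither rule. The percentages above describe likely misreadings of the output, not error rates of the plan.
- *Baseline CPAQ and centre go unused.* Baseline CPAQ enters the change score, and centre is used in the summaries of credibility, attendance and recruitment. Neither is a covariate in a stated CPAQ analysis, which is the narrower and correct point.
- *No adjusted analysis exists.* The remark about a pain covariate suggests that one was intended. The full protocol or analysis plan may set it out, including that the baseline value is used. What can be said is that the analyses described in the article have no place for it.

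It is also fair that proof of principle is one of five primary objectives, and that nothing makes CPAQ the sole basis for proceeding. That limits the weight of the point without removing it.

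**Conclusion.** The point holds as a mismatch between a comparative primary objective and a stated output given arm by arm. Its size is the gap between what the reader will see, about ±0.37 SD around each arm's change, and the uncertainty of the contrast that matters, about ±0.52 SD at 30 per arm (0.35 and 0.48 at 34). These figures assume equal SDs of change. The 15% to 25% range also assumes an equal true change of 0.2 to 0.5 SD and a reader who judges by which interval excludes zero. The mismatch itself depends on none of these assumptions. It does not affect the design, the data collected or the sample size, and it can be corrected before the data are analysed. Whether to define a smallest worthwhile difference, and whether to soften the abstract's word for showing proof of principle, are separate questions on which this point does not rest.

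**What to change.** In Planned analyses, make the proof-of-principle estimate the CCBT minus TAU difference in three-month CPAQ with its 95% confidence interval. Take it from a linear model with treatment, baseline CPAQ, baseline BPI pain interference and centre. Do the same for the AAQ-II, the other listed proof-of-principle measure, for which that section names no analysis. Keep the within-arm mean changes as description. Add no hypothesis test and make no power claim. The model also gives the promised pain covariate a place, with the baseline value specified.

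The cost is one regression per measure and a short change of wording. Table 1 shows that CPAQ, AAQ-II and the full BPI are already collected at baseline and three months, so no extra patients or assessments are needed. The drawback is that the headline interval will be wider than either within-arm interval, and the claim it supports more modest.
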